### 2.4 Treatment

Routine treatment includes antibiotics, probiotics, vitamins, antidiarrheal drugs, enteral nutrition, and endoscopic argon plasma coagulation according to the current practice guideline (Wang and Wang, 2018). These drugs and procedures are selected based on the patients’ disease conditions and their availability at each site.

Local glucocorticoids refer to retention enema of dexamethasone 10 mg combined with 100 mL of 0.9% sodium chloride injection once daily for a duration of 7 days. It requires the solution to be retained in the bowel for more than 1 h.

### 2.5 Study endpoints

The primary endpoints include the recovery and improvement of ARII after treatment. The secondary endpoints include the recurrence and aggravation of ARII, and adverse events during hospitalization and follow-up periods.

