**Methods:**

Overall, 60 patients with ARII will be enrolled. Eligible patients will be stratified according to the grade of ARII and randomly assigned at a ratio of 1:1 to the routine treatment alone and in combination with local glucocorticoids groups. The primary endpoints include the recovery and improvement of ARII. The secondary endpoints include the recurrence and aggravation of ARII and adverse events of glucocorticoids.

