### 2.3 Randomization, assignment, and blinding

Participants are stratified according to the grade of ARII at admission, and then randomly assigned to routine treatment alone and in combination with local glucocorticoids groups at a ratio of 1:1 within each stratum. The randomization sequence will be generated by computer system. The trial-group assignments are open-label to the participants and physicians.

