### 2.6 Sample size calculation

Sample size is calculated by using significant difference test in the proportion between two groups on the statistical software PASS 15.0.5 (NCSS, LLC. Kaysville, Utah, United States). The rates of improvement of ARII are estimated as 97.7% and 72.1% in patients treated with and without glucocorticoids according to the results of a previous study by Chen et al. (2021) An alpha value of 0.05, a power of 80%, and a dropout rate of 10% are set. Finally, 30 patients will be required for each group.

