### 2.15 Data analysis

The intention-to-treat (ITT) set comprises all participants randomized. The per-protocol (PP) set consists of participants who complete the assigned treatments of protocol and develop the primary endpoint events without major protocol violation. The safety set contains participants who receive at least one dose of local glucocorticoids and undergo at least one safety evaluation. Continuous variables are described as mean ± standard deviation and median (range) and categorical variables are described as frequencies (percentages). Whitney U test, chi-square test, and Fisher’s exact test are used, if appropriate. A two-sided P value of <0.05 is considered statistically significant. All statistical analyses are performed using IBM SPSS 26.0 software (IBM Corp, Armonk, NY, United States).

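### Recovery and improvement are both primary under one unsplit 0.05 threshold, while the sample size spends all of that 0.05 on improvement; if either endpoint can carry the claim, the false-positive rate is up to about 10%

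*Protocol article*

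**What the plan says.** The abstract of the protocol article says "The primary endpoints include the recovery and improvement of ARII", and section 2.5 repeats the pair: "The primary endpoints include the recovery and improvement of ARII after treatment". Section 2.7 defines them separately. Recovery needs both symptoms and mucosal damage to be gone. Improvement needs symptom relief or a fall of at least one grade in the Vienna rectal score. As worded, a recovered patient also counts as improved, so recovery is nested in improvement.

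Section 2.6 sizes the trial on one of the two: "The rates of improvement of ARII are estimated as 97.7% and 72.1% in patients treated with and without glucocorticoids". On the design parameters it says "An alpha value of 0.05, a power of 80%, and a dropout rate of 10% are set", and it concludes "Finally, 30 patients will be required for each group". It uses no recovery rate.

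Section 2.15 says "A two-sided P value of <0.05 is considered statistically significant" and lists chi-square and Fisher's exact tests, to be used as appropriate. It gives no other threshold and no order of testing.

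**The concern.** Two primary endpoints need a rule that links them to the trial's conclusion. The article fixes three things that do not fit together without one: two primary endpoints, one unsplit 0.05, and a sample size that has already spent all of that 0.05 on improvement.

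- If a significant result on either endpoint makes the trial positive, there are two chances of a false positive and the 5% is not held.
- If both must be significant, the 5% is held, but the 80% power describes improvement only. The chance of winning on both cannot be higher than the chance of winning on improvement, and it is not known.

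Either way, one of the two design properties stated in section 2.6 does not belong to the trial as its endpoints are written. With 60 open-label patients and no fixed order, whichever endpoint fell below 0.05 could be presented as the main result.

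**Working it through.** **Inputs from the article.** Improvement 97.7% vs 72.1%, alpha 0.05 two-sided, power 80%, dropout 10%, 30 per group (sections 2.6 and 2.15); allocation "at a ratio of 1:1 within each stratum" (section 2.3). **Assumed, because the article gives no recovery rate:** recovery 10% to 50%. Under the null, improvement is taken as 72.1% or 85% in both arms.

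**1. The plan's own figure.** Two-proportion z-test with unpooled variance:

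n = (1.960 + 0.842)² × (0.977×0.023 + 0.721×0.279) / 0.256² = 26.8, so 27 evaluable; 27/0.90 = 30 per group.

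The stated size reproduces exactly, for improvement alone at the full 0.05.

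**2. Either endpoint suffices: bounds.** The sum bound is 0.05 + 0.05 = 10%. For independent tests it is 1 − 0.95² = 9.75%.

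**3. Either endpoint suffices: simulation.** Null trials with 30 per arm and recovery nested in improvement; chance of at least one p < 0.05:

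| Test used | Recovery assumed | Result |
|---|---|---|
| Uncorrected chi-square for both | 30% to 50% | 8.8% to 9.8% |
| Fisher when an expected count is below 5, otherwise chi-square | 10% to 50% | about 3% to 9% |
| Fisher for both | 10% to 50% | 2.7% to 4.9% |

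The rule in the middle row is a common convention and an assumption here. Its upper end, about 9%, is at improvement 72.1% and recovery 30% to 50%. Its lower end is at improvement 85% and recovery 10%. The expected counts per arm there are 30 × 0.15 = 4.5 and 30 × 0.10 = 3, so both endpoints go to Fisher's test and the result is 2.7%. If the rule is applied to each observed table instead, that scenario gives about 4%.

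With chi-square and recovery of 10% to 20%, some scenarios come out slightly above 10% (10.4% at 30 per arm with improvement 85% and recovery 10%). The uncorrected test itself runs a little over 5% in samples of this size.

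**4. Both required.** Each test is at 0.05, so the error is at most 5%. Joint power cannot be computed without a recovery rate. As an illustration only, if recovery also had 80% power, joint power would lie between 0.80 + 0.80 − 1 = 60% and 80%.

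**5. Splitting alpha to 0.025 each.** By the formula in step 1:

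n = (2.241 + 0.842)² × 0.2236 / 0.256² = 32.4, so 33 evaluable; 33/0.90 = 36.7, so 37 per group (74 in total).

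If the trial stays at 27 evaluable per group, exact power for improvement goes from 84.7% to 74.5% with uncorrected chi-square, and from 63.4% to 61.9% with Fisher's test.

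**The case against.** **A success rule and testing order commonly sit in the analysis plan.** None is shown, and a journal article condenses its protocol. This stands as far as it goes: the lack of a multiplicity procedure would not be a finding by itself. What remains is what the article does fix. A later split of alpha would contradict section 2.6, because 30 per group rests on the undivided 0.05. A later both-must-win rule would leave the 80% describing one endpoint only. A fixed order with improvement first would fit section 2.6, but it would change the equal standing that the abstract and section 2.5 give the two endpoints.

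**A reader might infer that the trial has a 10% false-positive rate.** The documents do not support that. They nowhere say that either endpoint alone makes the trial positive, and the 0.05 in section 2.15 is a general threshold. Ten percent is a conditional ceiling. At the planned rates, 27 per arm gives (0.023 + 0.279)/2 × 27 = 4.1 expected non-improvers per arm, so under the usual convention Fisher's test would probably be used for improvement. Fisher's test for both endpoints keeps the error at or below about 5%. That protection comes from the test being conservative and from a choice the article leaves open, so it does not replace a stated rule.

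**A reader might also infer that splitting alpha always costs about ten points of power.** That holds for uncorrected chi-square only; with Fisher's test the loss is 1.5 points. Nor is the sample size miscalculated: it reproduces for improvement.

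**Conclusion.** The point holds in conditional form. Two primary endpoints, one unsplit threshold and sizing on only one of them are all in the text. If either endpoint can carry the claim, the false-positive rate is up to about 10%, and its actual value depends on the test used and on recovery rates that the article does not give. If both are required, the error is controlled but the power of the trial is unknown and cannot exceed that for improvement.

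This is a should-fix. No stated figure is wrong, and a short clarification resolves the matter, but it should be settled before outcome data are examined by arm.

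**What to change.** In section 2.5 and the abstract, name improvement as the single primary endpoint, since it is the one that was sized. Make recovery the first secondary endpoint, tested at two-sided 0.05 only if improvement is significant at two-sided 0.05 (fixed sequence). If improvement is not significant, recovery is reported descriptively.

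This holds the overall error at 5%, keeps 30 per group and loses no power for improvement. It needs a one-sentence amendment.

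The cost is that recovery can no longer carry the claim alone. Recovery is the stricter endpoint, whereas improvement can be met on symptom relief alone in an open-label trial, so the sponsor should accept that trade-off knowingly. Other repairs also work but cost more: an equal split of alpha needs 37 per group by the formula that reproduces the 30, and requiring both endpoints needs a recovery rate and a joint power calculation.

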### 2.6 Sample size calculation

Sample size is calculated by using significant difference test in the proportion between two groups on the statistical software PASS 15.0.5 (NCSS, LLC. Kaysville, Utah, United States). The rates of improvement of ARII are estimated as 97.7% and 72.1% in patients treated with and without glucocorticoids according to the results of a previous study by Chen et al. (2021) An alpha value of 0.05, a power of 80%, and a dropout rate of 10% are set. Finally, 30 patients will be required for each group.

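### The 80% power behind 30 patients per group holds for an unpooled z-test; under the usual chi-square/Fisher convention it is about 65% with 27 evaluable per group and 74% with all 30

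*Protocol article*

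**What the plan says.** Section 2.6 of the protocol article describes the method as "Sample size is calculated by using significant difference test in the proportion between two groups", run in PASS. It names neither the test option nor the variance form. The inputs are "The rates of improvement of ARII are estimated as 97.7% and 72.1% in patients treated with and without glucocorticoids" and "An alpha value of 0.05, a power of 80%, and a dropout rate of 10% are set". The result is "Finally, 30 patients will be required for each group".

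Section 2.15 covers the tests for all variables in one sentence: "Whitney U test, chi-square test, and Fisher’s exact test are used, if appropriate". It sets the level with "A two-sided P value of <0.05 is considered statistically significant". No switch point between chi-square and Fisher is given, and no other test for a binary endpoint is named. The intention-to-treat set is everyone randomised. Section 2.3 stratifies randomisation by ARII grade, with allocation "in combination with local glucocorticoids groups at a ratio of 1:1 within each stratum", and the trial is open-label.

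**The concern.** With a control rate of 72.1% and a treated rate of 97.7%, very few patients fail to improve. In such sparse tables the standard tests for two proportions can differ widely in power. A sample size derived from one test does not carry its power over to another.

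Section 2.6 states a power without naming its test. Section 2.15 names two tests whose power differs by about 20 percentage points at this sample size. If the conventional rule is followed, the risk of missing the assumed effect is about one in three with 27 evaluable per group, not the stated one in five. A non-significant result would then be read as stronger evidence against benefit than it is. With the choice left open in an open-label trial, the test could also be picked after the table is seen.

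**Working it through.** **Inputs.** Rates 0.977 and 0.721, power 80%, dropout 10% and 30 per group come from section 2.6. Two-sided 0.05 comes from section 2.15, and 1:1 allocation from section 2.3. Assumption: Fisher's exact test is used when the smallest expected count is below 5, and uncorrected Pearson chi-square otherwise.

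**Reproducing the 30.** Unpooled z formula:

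n = (1.96 + 0.8416)² × [p1(1−p1) + p2(1−p2)] / (p1−p2)²

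- Variance term: 0.977 × 0.023 + 0.721 × 0.279 = 0.2236
- Squared difference: 0.256² = 0.0655
- n = 7.849 × 0.2236 / 0.0655 = 26.8, so 27 evaluable per group
- Dropout: 27 / 0.9 = 30

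The approximate power of this test at 27 is 80.3%. The plan's figure is reproduced exactly.

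**How sparse the table is.** Expected non-improved patients at 27 per group: 27 × (0.023 + 0.279) = 8.2 in total. Under equal group sizes the smallest expected count is half of that, about 4.1. At 30 per group it is 30 × 0.302 / 2 = 4.5. Both are below 5.

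**Exact power.** This sums the two binomial distributions over all possible tables, counting those with P below 0.05:

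| Test | 27 per group | 30 per group |
|---|---|---|
| Fisher throughout | 63.4% | 72.1% |
| Fisher if expected count below 5, else chi-square | 65.5% | 74.4% |
| Uncorrected chi-square throughout | 84.7% | 88.3% |

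Under the rule, Fisher is selected in 72% of trials at 27 per group and 58% at 30. If an expected count of exactly 5 also sends the table to Fisher, the rule's power at 30 is 72.4%. A Yates-corrected chi-square throughout at 27 gives the same 63.4% as Fisher. The unrounded rates in the Discussion (97.67% and 72.09%) give 65.4% for the rule at 27.

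**One table that shows the gap.** Take 1 of 27 against 7 of 27 not improved, so the expected count is 4 per group.

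- Chi-square = 54 × (1×20 − 7×26)² / (27 × 27 × 8 × 46) = 5.28, P = 0.022
- Fisher's two-sided P = 2 × [C(27,8) + 27 × C(27,7)] / C(54,8) = 2 × 26,196,885 / 1,040,465,790 = 0.0504

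The same data are significant by one listed test and not by the other.

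**A stratified alternative.** Simulated Cochran-Mantel-Haenszel test at 27 per group, with assumed grade splits of 18/9 or 14/13 per group and overall rates near the design values: power about 84% to 85% and size about 5% without continuity correction. With the correction, power falls to about 64%.

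**The case against.** The strongest reply is that the plan contains no miscalculation. The 30 follows from a recognised formula with a proper dropout adjustment, and one of the two listed tests more than delivers 80%. The sentence in section 2.15 is generic and fixes no switch point, and naming the primary test is often left to a statistical analysis plan, which is not shown here. All of this is true, and it limits the finding: the switch at 5 is the reviewer's assumption, and the shortfall depends on it. It does not remove the finding. The stated power survives only if the uncorrected chi-square is used whatever the counts, and listing Fisher as an alternative points the other way.

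Several stronger readings are tempting but unsupported:

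- **That the sample size is arithmetically wrong.** It is not.
- **That power is 65% with 30 analysed per group.** The 65% belongs to 27 evaluable; with all 30 analysed the rule gives 74%.
- **That a pooled formula would have needed 30 evaluable and 34 enrolled, so chi-square itself is underpowered.** Exact power of the uncorrected chi-square at 27 is 84.7%. The loss comes from Fisher alone.
- **That the planned procedure has a true size of only 1.4% to 2.4%.** Those figures are for Fisher throughout, at common rates of about 85% and 72.1%. The rule gives 2.7% and 5.4%.
- **That power falls further because dropouts count as failures under intention-to-treat.** The article sets no such rule.

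**Conclusion.** The point stands as a mismatch between the sizing and the listed analysis. Under the conventional reading of section 2.15, power at the design rates is about 65% with the planned 27 evaluable per group and 74% if all 30 contribute, against a stated 80%. With Fisher throughout it is 63% and 72%. These figures rest on the design rates being true, a two-sided 0.05 level and the assumed switch at an expected count of 5. If the intended primary test is the uncorrected chi-square regardless of small counts, the claim is met (85% at 27), and the only defect is that the article does not say so.

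**What to change.** Choose one of two wording changes. Neither alters enrolment.

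1. In section 2.6, name the unpooled z-test as the basis of the 30 and restate the power as about 65% (27 evaluable per group) to 74% (all 30) for the chi-square/Fisher rule, with the switch point written into section 2.15.
2. In section 2.15, before any outcomes are seen, name one primary test that supports the 80%. A Cochran-Mantel-Haenszel test stratified by ARII grade is preferable because it matches the stratified randomisation. State explicitly that no continuity correction is applied, and confirm which form the named software reports, because the correction alone brings power down to about 64%.

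The first option costs a less favourable stated power. The second relies on an asymptotic test with few non-improved patients; Fisher's exact test can be reported alongside as a sensitivity analysis.

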### 2.7 Diagnosis, grade, and definitions

The diagnosis of ARII is mainly based on the comprehensive analysis of clinical, endoscopic, imaging, and histopathological manifestations after excluding infectious and other non-infectious enteritis. Notably, a history of radiotherapy for pelvic malignant tumors is a required diagnostic criterion.

The grade of ARII refers to the radiation injury classification proposed by the Radiation Therapy Oncology Group (RTOG) and the European Oncology Radiation Therapy Group (EORTG) (Cox et al., 1995), as follows.(1) Grade 0 is defined as no abdominal symptom.(2) Grade I is defined as increased frequency of defecation, loose stools, and/or rectal discomfort not requiring medication.(3) Grade II is defined as diarrhea requiring parasympatholytic drugs; and/or rectal secretion not requiring sanitary pads; and/or abdominal or rectal pain requiring analgesic drugs.(4) Grade III is defined as diarrhea requiring parenteral nutrition support; and/or secretion or hematochezia requiring sanitary pads; and/or abdominal distension showing dilatation of intestinal loop on abdominal X-rays.(5) Grade IV is defined as acute or subacute intestinal obstruction, fistula, or perforation; and/or hematochezia requiring blood transfusion; and/or abdominal pain requiring gastrointestinal decompression or surgical intervention.

The grade of intestinal mucosal damage on colonoscopy is evaluated in accordance with the Vienna rectal score (Wachter et al., 2000), as follows.(1) Grade 0 is defined as only localized mucosal hyperemia and edema.(2) Grade 1 is defined as diffuse non-confluent mucosal hyperemia and edema with single telangiectasia but without ulcer, stenosis, and necrosis.(3) Grade 2 is defined as diffuse and confluent mucosal hyperemia and edema with multiple non-confluent telangiectasia but without ulcer, stenosis, and necrosis.(4) Grade 3 is defined as unlimited mucosal hyperemia and edema with multiple and confluent telangiectasia, and the area of superficial ulcer is less than 1 cm^2^, but without stenosis and necrosis.(5) Grade 4 is defined as unlimited mucosal hyperemia, edema, and telangiectasia, and the area of superficial ulcer is more than 1 cm^2^, and the diameter of lumen diameter is more than 2/3 of the regular lumen diameter, but without necrosis.(6) Grade 5 is defined as unlimited mucosal hyperemia, edema, and telangiectasia with deep ulcer, fistula, or perforation, and the diameter of lumen diameter is less than 1/3 of the regular lumen diameter, and presence of necrosis.

Recovery is defined as patients’ clinical symptoms and intestinal mucosal damage on colonoscopy disappear. Improvement is defined as patients’ clinical symptoms alleviate or the Vienna rectal score decreases at least one grade.

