Most of patients with ARII present with mild symptoms and do not require medical care, but 5%–15% of them have to terminate radiotherapy due to severe discomfort, and even develop complications (Hauer-Jensen et al., 2004). In a previous RCT, Chen et al. demonstrated anti-inflammatory effects of glucocorticoids on ARII (Chen et al., 2021). Sixty-eight patients with ARII were randomly assigned to receive either dexamethasone combined with montmorillonite retention enema or oral montmorillonite. Inflammatory cytokines (IL-2 and IFN-γ) levels significantly decreased after treatment, with a more pronounced advantage observed in patients receiving combination dexamethasone (P < 0.001). They also demonstrated more significant response to treatment in terms of clinical improvement (97.67% vs. 72.09%, P < 0.001) and mucosal repairment under colonoscopy (93.02% vs. 65.12%, P < 0.001). Therefore, Chen et al. concluded that patients with ARII could receive more benefits from dexamethasone combined with montmorillonite. However, the evaluation of mucosal repairment, an important criterion for efficacy, was subjective, and lacked detailed descriptions. By contrast, another RCT by Kochhar et al. found a better efficacy of sucralfate than glucocorticoids (Kochhar et al., 1991). Thirty-seven patients were randomly assigned to receive either prednisolone enema combined with oral sulfasalazine or sucralfate enema. Although both two regimens were effective for alleviating clinical symptoms, prednisolone combination treatment was inferior to sucralfate (53.3% vs. 94.1%, P < 0.05). In terms of endoscopic improvement, there was no significant difference between the two groups (46.7% vs. 70.5%, P > 0.05). But two patients withdrew from the trial due to intolerable myalgia and headache in prednisolone enema combined with oral sulfasalazine treatment group. Considering the safety and low cost of sucralfate, Kochhar et al. preferred sucralfate as the better choice for RII (Kochhar et al., 1991). Notably, some of the patients included in the study by Kochhar et al. had CRII with intestinal tissue fibrosis, where anti-inflammatory effects of glucocorticoids might be unsatisfactory.

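### The 80% power was worked out from clinical-improvement rates, but improvement is defined as symptoms or a one-grade Vienna fall; for that endpoint the power is unsupported and probably lower

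*Protocol article*

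**What the plan says.** Section 2.5 makes improvement part of the primary outcome: "The primary endpoints include the recovery and improvement of ARII after treatment". Section 2.7 defines it with two alternative limbs: "clinical symptoms alleviate or the Vienna rectal score decreases at least one grade".

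The sample size in section 2.6 rests on one pair of rates, taken from an earlier randomised trial: "The rates of improvement of ARII are estimated as 97.7% and 72.1% in patients treated with and without glucocorticoids". It adds: "An alpha value of 0.05, a power of 80%, and a dropout rate of 10% are set". The result is 30 patients per group.

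The Discussion describes that same earlier trial and gives two separate results for it: "clinical improvement (97.67% vs. 72.09%, P < 0.001" and "mucosal repairment under colonoscopy (93.02% vs. 65.12%, P < 0.001". The planning pair is the first of these, rounded. The article gives no rate for the two limbs combined and nothing on how far they overlap.

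**The concern.** The sample size uses the source trial's clinical result, while the analysis will also count patients who improve only on endoscopy. Adding a second route to success cannot lower a response rate, and the two arms do not have the same room to rise. In the control arm 27.9% are clinical non-responders and could be added by the endoscopic limb; in the glucocorticoid arm only 2.3% could. The likely effect is that the control rate moves up towards a treated rate already near the ceiling, and the 25.6-point planned difference shrinks. With 60 patients there is little reserve, so a real effect on symptoms could be missed because the definition of success is wider than the one that was powered.

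**Working it through.** **Inputs.** Clinical improvement 97.67% versus 72.09% and mucosal repair 93.02% versus 65.12% (Discussion); 97.7% versus 72.1%, alpha 0.05, power 80%, dropout 10%, 30 per group (section 2.6); two-sided testing with chi-square or Fisher's exact test (section 2.15).

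**Reproducing the plan's figure.** The two-proportion Z formula with unpooled variance is n = (1.960 + 0.842)² × [p₁(1−p₁) + p₂(1−p₂)] / (p₁−p₂)². With p₁ = 0.977 and p₂ = 0.721:

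- variance sum = 0.0225 + 0.2012 = 0.2236
- n = 7.849 × 0.2236 / 0.256² = 26.8, so 27 per arm
- 27 / (1 − 0.10) = 30 per arm, as stated.

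The arithmetic is right for its inputs. The question is what the inputs measure.

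**Limits on the either/or rate.** P(symptoms or Vienna) = p + q − P(both), where p is the clinical and q the mucosal rate. It is lowest when one limb is nested in the other:

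- control: at least 72.1%, at most 100% (room 27.9 points)
- glucocorticoid: at least 97.7%, at most 100% (room 2.3 points).

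**Scenarios.** Assumptions: the source's mucosal rates stand in for a one-grade Vienna fall, and the correlation phi between limbs is the same in both arms. Then P(both) = pq + phi × √[p(1−p)q(1−q)], which cannot exceed the smaller of p and q.

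- Control: pq = 0.4695, square-root term = 0.2138. At phi 0.5, P(both) = 0.5763, so the composite is 0.7209 + 0.6512 − 0.5763 = 79.6%.
- Glucocorticoid: pq = 0.9085, square-root term = 0.0384. At phi 0.5, P(both) = 0.9277, so the composite is 0.9767 + 0.9302 − 0.9277 = 97.9%.

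With these rates phi cannot exceed 0.85 in the control arm or 0.56 in the glucocorticoid arm, so 0, 0.25 and 0.5 are all attainable in both. The nested row sets the overlap at its maximum in each arm.

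Power is from full enumeration of both binomial distributions at 27 per arm, two-sided 0.05, chi-square without continuity correction:

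| Overlap of the limbs | Control | Glucocorticoid | Difference (points) | Chi-square | Fisher |
|---|---|---|---|---|---|
| Fully nested (the plan's rates) | 72.1% | 97.7% | 25.6 | 85% | 63% |
| phi 0.5 | 79.6% | 97.9% | 18.3 | 64% | 34% |
| phi 0.25 | 84.9% | 98.9% | 14.0 | 49% | 17% |
| Independent (phi 0) | 90.3% | 99.8% | 9.6 | 26% | 4% |

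**A check that does not use the mucosal rates.** Suppose a quarter of control symptom non-responders gain a Vienna grade and the treated rate stays at 97.7%. The control rate is 0.7209 + 0.25 × 0.2791 = 79.1%, and power is about 64% / 34%. If half do, the control rate is 86.0% and power is 34% / 10%.

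**Which test.** At the planned rates the expected number of non-responders per arm is 27 × [1 − (0.977 + 0.721)/2] = 4.1. That is below 5, so Fisher's test may well be the one used.

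**The case against.** Several points against this are sound and limit what can be claimed.

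- A reader might infer that the control rate is simply understated. The article does not show that. If every endoscopic responder is also a symptom responder, the composite equals 72.1%. The overlap is unreported, so at least 72.1%, and probably higher, is as far as the text goes.
- A reader might also infer that the planned difference survives only under full nesting. That is false. A control rate of 74.4% against 100% still differs by 25.6 points without nesting, and exact power is then 94% / 72%. It is a boundary case, but it rules out the stronger statement.
- The Fisher figures should not be charged wholly to the either/or definition. Fisher power is already 63% at the plan's own rates. The effect of the definition is the drop from the nested row.
- The proxy is weak. Mucosal repair in the source trial is not a one-grade Vienna fall, and the Discussion itself calls its assessment subjective and thinly described. Independence is the extreme scenario and hardly the likeliest for two signs of the same injury.
- Colonoscopy is repeated only at months 3 and 12 (section 2.12). If the endpoint were read at day 7, only symptoms would be available and the second limb would add nothing. The article does not fix the time.
- Whether endoscopy entered the source trial's clinical response cannot be seen from here. The Discussion's separate reporting favours distinct measures, but that is an inference.
- It is tempting to add that one patient could be both improved and aggravated. The article does not define aggravation, so this cannot be shown.

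What stands is that the rates are labelled as clinical improvement, the endpoint is wider, and nothing links the two.

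**Conclusion.** The concern holds in this form: the stated 80% power was not derived for improvement as section 2.7 defines it, and for that endpoint it is unsupported and probably lower. The probable direction follows from the unequal room to rise. The size depends on an overlap that the article does not give. Under the stated proxy and equal-correlation assumptions, chi-square power at 27 per arm runs from 85% (nested) through 64% and 49% to 26% (independent), and Fisher power from 63% through 34% and 17% to 4%. A moderate departure from nesting is enough to take chi-square power clearly below target. The figure of 30 per group is not an arithmetic error.

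**What to change.** Make the planning rate and the endpoint describe the same event. There are two ways.

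1. Keep the either/or definition in section 2.7. In section 2.6, give justified composite rates for both arms and restate the power of 30 per group as a range over them. Cost: some text, and a less favourable stated power.
2. Name symptom improvement at a fixed visit as the powered primary endpoint in sections 2.5 and 2.7, and report the month-3 Vienna fall separately. Cost: patients who improve only on endoscopy no longer count as primary responders, and the primary result rests on symptoms in a trial that section 2.3 describes as open-label to participants and physicians. That bias risk should be weighed before choosing this route.

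Either is a change of wording and calculation. Neither by itself requires a new sample size, but the first may show that one is needed: under independence, about 80 evaluable per arm by the pooled Z formula, or 80 / 0.9 = 89 with dropout.
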